**2. Information concerning the project**

2:1 Summary of the research project

Poor dietary habits and inadequate physical activity means that many children and adolescents run the risk of becoming overweight and developing disordered eating habits (irregular and/or restricted eating as well as body dissatisfaction). Childhood obesity is 3-5 times more common in families with low income and/or education compared to those with high. The prevalence of overweight is increasing and effective prevention measures are in demand. Data from Stockholm county from 2006-2007 indicates that the prevalence of overweight among children is probably stabilising or even decreasing in affluent areas, but the trend seen in more deprived areas is in the opposite direction. Strategies that promote healthy and regular eating habits and physical activity are believed to have the potential to prevent both overweight and disordered eating and promote healthy weight development among children and adolescents.

The school arena has the potential to even out health inequalities that may arise due to the different social, cultural and health behaviours of parents. Previous research has shown that prevention is more effective when community activities are complemented with home-based strategies. Given the uneven distribution of health inequalities and obesity which affects deprived groups disproportionally, the potential for prevention is great.

The home environment and parental behaviour have an important influence on children’s dietary habits. There is evidence that active parental encouragement and support is important for the development of good physical activity habits.

The school health care system is probably one of the best channels through which to reach parents concerning their children’s health development. At the health check-up conducted in the pre-school year, parents are present. This is an ideal opportunity to present a clear, consistent message to parents about health and attitudes. Our experience is that school health staff are very engaged and motivated regarding issues of dietary habits and physical activity, but that resources for preventive work is scarce. Staff are interested in learning more about the technique “motivational interviewing (MI)”. MI has been shown to be effective in helping people make changes to their dietary and physical activity habits in the clinical setting but this has yet to be thoroughly tested in the school setting.

We will study whether it is possible to improve children’s dietary and physical activity habits and weight development by conducting motivational interviews with parents through the school health care system and by the use of teacher-led classroom-based activities.

Aim

To develop and evaluate a parental support programme delivered in the school health care setting to promote healthy dietary and physical activity habits for parents of 6-year-old children.

Research questions:

How does motivational interviewing with parents, in combination with teacher-led classroom activities, affect children’s dietary habits, physical activity levels, weight development and parental self-efficacy to affect change?

Do children’s dietary habits, physical activity, body weight index (BMI) and parental self-efficacy differ by parental education level?

Research variables:

We aim to study 200 children in 16 pre-school classes in deprived areas in the municipality of Nacka. Half of the classes will be randomised to the intervention group and the other half to the control group.

The primary outcome will be the consumption frequency of certain indicator foods (fruit, vegetables and energy-dense foods) as assessed by questionnaire.

Using an accelerometer, physical activity will be evaluated as total step count per day, the average time in total physical activity over a week, the number of minutes at different intensities and time spent sedentary.

A qualitative study with parents and teachers will be conducted using focus groups and will be analysed using content analysis.

Parental self-efficacy (the ability to affect change and the belief that they are in control) will be evaluated using questions taken from the social cognitive theory.

Secondary outcomes include weight and length data obtained from the school health care journals. Waist circumference is also measured during the school health check-up. Body mass index (BMI) is calculated and overweight and obesity are identified using international cut-offs. In addition, BMIsds is calculated based on Swedish cut-offs.

Knowledge gains:

The school health care system lacks effective and evaluated tools for use in their communication with children and their parents. There is a demand for more resources to use in health check-ups but to the best of our knowledge, no studies have been conducted that show the effectiveness of such resources. The project could generate new ways for both teachers and school health care staff to work to promote health and reduce health inequalities among children. When the project is completed the method can be spread to other municipalities and regions.

School health care staff are very interested in learning about MI and becoming trained in its use. The results from our study are likely to be integrated into their usual routines. We hope that the study will show that with very meagre extra resources (for the MI), a relatively large effect on children’s lifestyle habits can be achieved. The pre-school year is a very suitable time to conduct a parental support programme as the children are still completely dependent on their parents and the classroom syllabus is very flexible. Only a few studies have examined parental support and children’s dietary and physical activity habits, and none has been carried out in Sweden that we know of.

2:2 What is/are the primary scientific question(s) forming the basis of the design of the

project?

Hypothesis: Motivational Interviewing in combination with teacher led classroom activities will promote healthy dietary and physical activity habits, weight development and parental self-efficacy to make changes.

2:3 State the results from relevant animal experiments (clinical trials):

N/A

2:4 Give an overview of the examination procedures used, data collection and the nature of

the data

The project will be carried out in collaboration with the school health care system in the municipality of Nacka, which has a long history of working with children and adolescent lifestyle behaviours. Nacka is a municipality with a relatively high median income and education level but also big differences in socioeconomic levels. Living conditions vary greatly between areas of the municipality and several health problems are a concern. One of these is childhood and adolescent overweight, which continues to increase. Our research group, which until recently belonged to Stockholm County Council, has a lot of experience with communicating health information and supporting local projects related to diet and physical activity in the county’s municipalities and organisations.

We aim to study 200 children in 16 pre-school classes in deprived areas in the municipality of Nacka. Half of the classes will be randomised to the intervention group and the other half to the control group.

The intervention consists of two motivational interviews three months apart for parents and teacher-led classroom activities for children.

During the spring of 2010, the principals of nine schools will be approached and invited to participate (Appendix 5:1). For the school to be included in the study, at least 30% of the families must be classified as deprived. Once the school has consented, the pre-school teachers will be invited. Parents will be informed (Appendix 5:1) at the regular parent-teacher meeting and a letter inviting them to participate will be sent at the beginning of the school term (Appendix 4). In order to reach the families the letter will be sent in tandem with the routine letter from the school health care. Parents consent to participate in the project by signing and returning the consent form (Appendix 4).

Baseline measurements of physical activity. Children will wear an accelerometer for a week. The physical activity is measured with an accelerometer which provides objective measures of different variables, such as total physical activity, sedentary time, total steps and time spent at different intensity levels. Accelerometry is a reliable method and has been used in many studies both nationally and internationally to measure children’s physical activity. The accelerometer will be given out by a member of the research team and collected after 7 days.

Baseline measurements of eating habits (intake frequency of fruit and vegetables and energy-dense products), physical activity habits, inactivity and sleep is assessed by means of a survey (Appendix 5:2). The survey questions are based in part on a validated English parent questionnaire. Parents' self-efficacy, ie, their confidence in their ability to be able to change their children's food and movement habits are measured by a questionnaire (Appendix 5:2). The questionnaire has been translated and modified for use in the area of food and physical activity based on a validated English questionnaire which measures parents' self-efficacy in parenting. Surveys are sent home to parents as soon as consent has been received by the researchers. The questionnaires are then handed in by the parents at the first motivational interview.

The intervention is planned to start in November. During the intervention, the teachers in the intervention classes follow a teacher's manual (Appendix 5:3) which is based on a brochure that has been designed as a result of a scientific review (www.folhalsoguiden.se / food). The brochure is designed to be educational, contains many illustrations and is written in simple Swedish (Appendix 5:4). It is based on the various themes of the review; 1. Good food and meals, 2. Movement/Physical Activity, 3. Candy, snacks, ice cream and soft drinks, 4. Fruits and Vegetables, 5. Advertising, TV and other media, and 6. Sleep and rest. The material contains facts and evidence-based advice to parents. The information in the brochure will form the basis for the future motivational interview. The brochure will be sent home to the families before the intervention starts, so that they have time to reflect on the content before the first motivational interview.

In the pre-school class the teacher will conduct 10 lessons (each 30 minutes in length) described in the teacher manual. Students will be assigned simple home exercises from a workbook on 7 occasions (Appendix 5:5). The purpose of the homework assignments is so that children remind their parents at home about the different themes that have been brought up at school.

During the routine health check-up (which assesses development progress, height, weight, immunisation status, etc.) in Nacka both a school physician and a school nurse are present together with the child and parents. Child's weight, height and waist circumference from the health check will be used in the study. In conjunction with the check-up, a person trained in motivational interviewing will conduct a 45-minute meeting with the parents. The conversation is based on the parents' needs and the content of the brochure. Goals for change will be formulated at the end of the meeting. Parents will be invited to a follow-up meeting after about three months, where they will discuss the changes that have been made. Parents will be given a diary to bring home in which they should record progress and goals met, every other week (Appendix 5:6). Text messages will be sent every other week as a reminder to fill in the diary. A text message will also be sent as a reminder of the scheduled MI meeting.

Our results will be based on questionnaires of the children's eating habits, and parents' self-efficacy assessed according to validated methods. Our conclusions about the children's physical activity will be based on objective measurement with accelerometers. Questionnaires, diaries and brochures will be pre-tested and adjusted if necessary before use in the study of a group of parents similar to the target audience. That the intervention is progressing as it should (compliance) will be checked by recording every twentieth motivational interview with the permission of the parents and (anonymously) coding them to ensure the quality of the motivational interviews. After each classroom lesson, the teachers will fill in a log/checklist so that we can check whether the teaching manual has been complied with and how much time the class has spent on each theme (intervention dose).

Randomisation will occur at school class level after baseline measurements have been made on all children. In the control classes the ordinary health check-up will be conducted as normal. No classroom activities or motivational interviewing will be offered. After the project is completed, all families in the control classes will be offered motivational talks and classes will have access to the brochures, teacher manual and workbook.

After the end of the intervention, after six months, the same measurements made at baseline will be made again. A lottery ticket will be offered to both the control and intervention families after the baseline measurements have been performed and another lottery ticket will be offered after the measurements at the end of the project have been made.

At the end of the intervention, 4 groups of parents (about 5-6 in each group) will participate in a focus group discussion with the aim of gaining an understanding the participants’ experience of the project. The discussion will be led by a researcher with extensive experience in focus group methodology. Focus group discussion is a method that is suitable for exploring people's experiences, perceptions, preferences or difficulties. The focus groups will be analysed using qualitative content analysis. Focus group discussions will also be conducted with teachers of the intervention classes to evaluate the classroom components and what obstacles and opportunities the teachers experienced.

A follow-up survey will be done a year after the start of the project with the same measurements at baseline and at the end of the project (questionnaires to parents about the child's eating habits, parental self-efficacy and measurement of the child's physical activity). The children will be weighed and measured again as part of the school health care system’s routines and the data will be collected by scientists from Karolinska Institutet.

An internal team of experts has collaborated to develop the materials in the project. A teachers' group of six teachers have helped to develop the teacher's guide and workbook for children. A steering committee comprising members from Karolinska Institutet, school health and public health planners from Nacka meet once a month to prepare and plan the project.

2:5 Describe how collected biological material is to be stored in a biobank:

N/A

2:6 Funding of the study:

This study is funded by the Public Health Fund, Stockholm County Council and the Signhild Engkvist Foundation.

2:7 Documentation, data protection and record-keeping:

All names and personal data will be replaced with a code number in order to de-identify participants. These code lists will be kept locked up. Lists of personal numbers, names, and addresses will be kept locked in a filing cabinet at Karolinska Institutet. Questionnaire and accelerometer data kept locked in a filing cabinet at Karolinska Institutet. Data on weight and height measurements will be collected by the project team from the school nurse and will be kept under lock. The de-identified data will be entered into a data file by the project team. The material that will be processed and analysed is guaranteed confidentiality. Throughout the project, the principal researcher and participating researchers will have access to the material. After completion of the project all collected material will be archived according to the prevailing rules at Karolinska Institutet.

2:8 Describe previous experience (your own and/or others’) of the procedure, technique or

treatment used:

The methods used in the present research are scientifically proven and established in the scientific community. The researchers in the project have collective experience and knowledge of these methods and have previously produced a number of reports, theses and articles. The project team has good knowledge and experience of working with questionnaires, accelerometers, focus groups, motivational interviewing and working with children in school-based projects. The project group has previously published reports and scientific articles that essentially apply the same methodologies chosen for this project. The principal investigator is, in consultation with a statistician, responsible for the statistical analysis and has extensive experience of school-based studies and analysis of children's physical activity, diet and weight development.

The concepts of weight development, overweight and obesity will not be mentioned to the children. The project focuses on delivering a positive health message which emphasises that good food and physical activity habits leads to children having more energy in school and getting a healthy start to school life.

No risk of complications for any of the methods proposed in this project have been identified through previous studies or in the existing literature.

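### The protocol has baseline questionnaires handed in at the first motivational interview, which contradicts its rule that randomisation follows baseline and leaves control families no stated hand-in route

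*Protocol*

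**What the plan says.** All the statements about timing are in section 2:4 of the protocol.

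- Sending out: "Surveys are sent home to parents as soon as consent has been received by the researchers".
- Return: "The questionnaires are then handed in by the parents at the first motivational interview".
- Randomisation: "Randomisation will occur at school class level after baseline measurements have been made on all children".
- Place of the interview in the design: "The intervention consists of two motivational interviews three months apart for parents and teacher-led classroom activities for children". For control classes: "No classroom activities or motivational interviewing will be offered".
- Brochure: "The brochure will be sent home to the families before the intervention starts", so that parents can think about it ahead of the first interview. Control classes get access to the brochures once the project is over.
- Setting of the interview: "In conjunction with the check-up, a person trained in motivational interviewing will conduct a 45-minute meeting with the parents". The child's weight, height and waist for the study come from that check-up.

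Section 2:4 also promises a lottery ticket to families in both arms once baseline is done. Section 4:2 describes a pre-paid envelope, but for the consent form.

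**The concern.** The value of a baseline in a randomised trial is that allocation cannot have influenced it. Here the stated return point for the questionnaires is itself an intervention session. If the sentence is followed, three things can go wrong.

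- **Exposure before completion.** The brochure covers food, sweets and soft drinks, fruit and vegetables, activity, media and sleep. The questionnaires ask about largely the same topics. A parent who completes the form late does so knowing the allocation and having had material that control parents have not.
- **Differential reporting.** These are unblinded parental reports. In the intervention arm they are handed over at the session where the family's own goals for change are set.
- **Differential missingness.** No return route is stated for a control parent, or for an intervention parent who does not attend the interview.

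The same measurements are repeated after six months and one year after the project starts. Any change score or baseline-adjusted comparison of the questionnaire outcomes would carry these faults. The analysis could not remove them afterwards, because without completion dates clean and exposed forms cannot be told apart.

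**Working it through.** The protocol gives no figure to reproduce. The check is to order the stated events in each arm and see whether the statements can hold together.

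1. **Can the first interview precede randomisation?** No. Interviews are part of the intervention and are not offered in control classes, so a class must be allocated before its families can be interviewed.
2. **Can the brochure precede randomisation?** Not if control classes get it only after the project. It goes home ahead of the first interview, so it falls between allocation and the hand-in.
3. **Resulting order**
   - Intervention arm: consent, questionnaire sent home, randomisation, brochure sent home, first interview with hand-in.
   - Control arm: consent, questionnaire sent home, randomisation, ordinary check-up. No hand-in is stated.
4. **Comparison with the randomisation rule.** The rule needs baseline complete on all children before allocation. Under the order in step 3, no questionnaire is in the team's hands by then in either arm. The hand-in sentence and the randomisation rule are therefore incompatible for the questionnaires.
5. **Is there another route?** The only postal return described is for the consent form (section 4:2). The control arm's check-up could serve, but questionnaire collection there is not mentioned.
6. **Which outcomes are touched?** Food frequency (primary in section 2:1), questionnaire-reported activity habits, inactivity and sleep, and parental self-efficacy. Section 3:3 names accelerometer-measured activity as primary and sizes the trial on it. Accelerometers are handed out and collected separately, so that outcome is not affected.
7. **Can the bias be sized?** Let Δ be the eventual arm difference, f the fraction of it already present in the recorded baseline, and b the slope of outcome on baseline. A change score then estimates Δ(1 − f), and a baseline-adjusted analysis estimates Δ(1 − f·b). The document gives neither f nor b. If every form is completed before allocation, f = 0 and there is no bias. If the brochure changes how parents report rather than what children eat, f could have either sign. No number follows.
8. **Weight, height and waist.** Both arms have the check-up, so the missing route does not apply. In the intervention arm the check-up is linked to the interview, and its date relative to randomisation is not stated.

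**The case against.** The strongest reply is that handing in is not filling in. Questionnaires go out on consent, the consent letter is sent at the start of the autumn term (section 4:1), and the intervention starts in November. Many forms could be completed well before allocation. The randomisation rule also states the right order, and the lottery ticket for both arms shows that baseline is meant to be collected from control families too. On this reading the hand-in sentence is a slip.

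Much of this stands, and it limits the point in four ways.

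- A reader might infer that every one of the roughly 100 intervention baselines is contaminated. The text supports only a late hand-in; how many forms are completed late is unknown.
- A reader might infer that control baselines will be missing. The text supports only that no route is stated.
- A reader might put a percentage on the dilution of the treatment effect. Neither interview can have had an effect by the hand-in, and nothing in the document fixes how much of the difference the brochure, or any early lessons, would produce.
- A reader might extend the bias to weight, height and waist. These come from the health check rather than from parental report, and both arms have the check-up. Only the unstated date remains.

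The contradiction itself survives. Early completion is possible but neither required nor recorded, and a stated intention to collect control baselines does not supply a way of doing so.

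**Conclusion.** The point holds as a contradiction within section 2:4 that must be reconciled, together with an unstated return route in the control arm. It does not prove that baseline will be measured after randomisation. Followed literally, the hand-in sentence gives a post-allocation hand-in in one arm and none in the other, for the food-frequency outcome and for self-efficacy. Baselines in the intervention arm can then be influenced by allocation and the brochure, and missingness can differ between arms. The size of the bias cannot be derived from the document and may be zero if parents complete the forms promptly.

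The conclusion rests on two readings: that interviews occur only in allocated intervention classes, and that control families do not get the brochure during the project. Section 2:4 supports both. How much the fault matters for the trial's main conclusion also depends on which of the two outcomes named as primary is meant. It matters directly under section 2:1, and not for the accelerometer outcome in section 3:3.

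**What to change.** Replace the hand-in sentence in section 2:4 with wording such as:

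*In both groups, parents return the baseline questionnaires with the accelerometer after the 7-day wear, or by pre-paid envelope. Parents write the completion date on the form. A fixed cut-off date for return is set before randomisation and before any brochure is sent. All classes are randomised after that date. Forms not returned by then count as missing baseline, and the child remains in the trial.*

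The cut-off keeps the existing rule that allocation waits for baseline, without letting one unreturned form hold up randomisation.

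For weight, height and waist, record the date of the check-up relative to randomisation. Call a value baseline only if it was measured before randomisation.

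The cost is some reminders before the cut-off and a few late forms lost as baseline. The protocol does not say who collects the accelerometers or whether parents are present, so the team should check whether that route needs an extra contact. A pre-paid envelope, already used for consent, is the fallback.

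### Baseline parent questionnaires are to be handed in at an interview that only intervention families have, and only after the randomisation they should precede

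*Protocol*

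**What the plan says.** All of the following is in Protocol section 2:4 unless another section is named.

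- **Sending out.** "Surveys are sent home to parents as soon as consent has been received by the researchers". No date for completing the form is given.
- **Return.** "The questionnaires are then handed in by the parents at the first motivational interview". No other route appears in the text.
- **What the interview is.** "The intervention consists of two motivational interviews three months apart for parents and teacher-led classroom activities for children".
- **Control classes.** They keep the ordinary health check-up. "No classroom activities or motivational interviewing will be offered". Their offer comes later: "After the project is completed, all families in the control classes will be offered motivational talks".
- **Randomisation.** "Randomisation will occur at school class level after baseline measurements have been made on all children".
- **Brochure.** "The brochure will be sent home to the families before the intervention starts, so that they have time to reflect on the content". Control classes get access to it only once the project is over.
- **Role of the questionnaire.** Section 2:1, under the research variables: "The primary outcome will be the consumption frequency of certain indicator foods", assessed by questionnaire. Section 3:3 instead names physical activity by accelerometry as primary and bases the sample size on it.

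**The concern.** A baseline value is useful in a randomised comparison because it is fixed before allocation and obtained in the same way in both arms. The stated return rule gives neither assurance for the parent-reported measures. Three things follow from it.

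1. Intervention parents can fill in or revise the form after learning their allocation, with the advice brochure already at home.
2. Intervention families who do not come to the first interview have no stated way to return a baseline form.
3. Control families have no stated way at all, so theirs must come back by some other route and at some other time.

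The first could move part of an early response into the baseline. The second could make the existence of a baseline depend on taking up the intervention, in one arm only. Once classes have been randomised, analysis cannot fully repair either.

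**Working it through.** **Sequence check**

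| Step | What section 2:4 requires | Consequence |
|---|---|---|
| 1 | Forms go home at consent | Early completion is possible but not required |
| 2 | Classes are randomised after baseline on all children | Forms should be in hand by now |
| 3 | Brochure goes home before the intervention starts | Intervention parents have the advice |
| 4 | First interview, intervention classes only | Must come after step 2 |
| 5 | Forms are handed in at step 4 | Contradicts step 2; impossible for controls |

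The offer of talks to control families comes after the project, so it cannot serve as a baseline hand-in point. Both arms are nevertheless meant to have a baseline: section 2:4 gives both a lottery ticket once those measurements are done. The accelerometer is handed out by the research team and collected after 7 days, so it is outside this problem.

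**Possible size**

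The protocol gives no SD, correlation or expected effect for the questionnaire. Its sample size (12 classes, about 144 children) concerns accelerometer steps and does not enter here. The inputs below are therefore assumptions: outcome SD 1, slope of follow-up on baseline β = 0.6, clustering ignored.

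*(a) Response already in the intervention baseline.* Let the true effect be δ = 0.30 SD and the shift in the intervention arm's baseline mean be d.

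- Baseline-adjusted estimate = δ − βd. For d = 0.10: 0.30 − 0.06 = 0.24. For d = 0.20: 0.30 − 0.12 = 0.18.
- Change-score estimate = δ − d: 0.20 and 0.10.
- Milder case: half the forms carry a quarter of the effect, so d = 0.5 × 0.25 × 0.30 = 0.0375. This gives about 0.28 adjusted and 0.26 by change score.
- If the brochure instead made parents report more critically, d would be negative and the estimate would be too large.

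*(b) Baseline missing for non-attenders in the intervention arm only, no true effect, complete-case baseline adjustment.* Suppose baseline and follow-up both reflect an underlying family habit (loading √0.6 on each), attendance propensity has correlation ρ with that habit, and the lowest fraction p does not attend. Then

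bias ≈ (1 − β) × √β × ρ × φ(z_p)/(1 − p).

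The last factor is 0.195, 0.350 and 0.497 for p = 10%, 20% and 30%.

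| Attendance depends on | p = 10% | 20% | 30% |
|---|---|---|---|
| Measured baseline value only | 0 | 0 | 0 |
| Underlying habit, ρ = 0.3 | 0.02 | 0.03 | 0.05 |
| Underlying habit, ρ = 0.5 | 0.03 | 0.05 | 0.08 |
| Underlying habit, ρ = 1 | 0.06 | 0.11 | 0.15 |

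In the last row the formula runs slightly low, because truncation flattens the fitted slope. Simulation gives about 0.06-0.07, 0.12 and 0.17-0.18. In the first row adjustment removes the bias, but a change score is biased by (β − 1) × 0.195 to (β − 1) × 0.497, that is −0.08 to −0.20.

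**The case against.** **Handing in is not completing.** Consent letters go out at the start of the autumn term and the intervention starts in November, so many parents may fill in the form weeks before allocation. This stands. A reader might infer that the baseline answers of all of about 100 intervention families are contaminated. The documents do not support that: the arm difference is certain for collection and only possible for content.

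**A return route may exist elsewhere.** The annexes, including the questionnaire and consent letter, are not in the English text, and the first interview is held together with the health check-up that control families also attend. A reader might infer that controls would have no baseline; the text shows only that no route is stated for them. Hand-in at the check-up would still leave intervention forms arriving after allocation, so the contradiction remains.

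**The primary outcome is disputed within the protocol.** It would go too far to say that the trial's primary analysis is compromised. If section 3:3 governs, the primary baseline is sound and the problem lies with the diet and self-efficacy outcomes.

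**The bias needs an analysis that the protocol does not fix.** This is correct. A comparison of follow-up values that keeps all families is untouched by either mechanism. The inputs are also generous: a shift of 0.10-0.20 SD places one to two thirds of a 0.30 SD effect before the first interview, across the whole arm, and nothing in the protocol supports that. The 0.17 SD figure is close to a worst case.

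**Conclusion.** The contradiction is certain and rests on the text alone. The return rule for the parent questionnaires cannot be reconciled with randomisation after baseline, nor with a control arm that has no interview. As written, collection of the parent-reported baseline, including the outcome that section 2:1 calls primary, depends on arm and falls after allocation in the intervention arm.

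That this would bias the result is a risk, not a demonstrated fact. Under the assumptions above, a baseline shift turns 0.30 SD into about 0.24-0.18 SD with adjustment or 0.20-0.10 SD with change scores. Selective loss of non-attenders adds a spurious benefit from 0 up to about 0.17 SD with complete-case adjustment. The two act in opposite directions, so the net sign and size cannot be known in advance.

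**What to change.** Replace the return sentence in section 2:4 with:

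> Baseline questionnaires are collected in both arms by the same route (at accelerometer collection after 7 days, or by pre-paid envelope) by a fixed deadline before classes are randomised and before the brochure is sent; parents record the completion date.

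Then:

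- Randomise at the deadline even if some forms are outstanding, and amend the sentence requiring baseline on all children to match. Otherwise one non-returning family could hold up the November start.
- Treat as missing baseline any form completed after allocation, and any undated form returned after it. A form dated before allocation but returned later is kept.
- Keep families with a missing baseline in the analysis.
- Use the same return route in both arms at the follow-up measurements.

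The means already exist: the research team collects the accelerometers (section 2:4), and a pre-paid envelope is used for consent (section 4:2). The cost is reminders before the deadline and some missing baselines.
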